## Abstract

**Background:**

Although the benefits of physical activity (PA) on to prevent and manage non-communicable diseases are well known, strategies to help increase the levels of PA among different populations are limited. Exercise-referral schemes have emerged as one effective approach to promote PA; however, there is uncertainty about the feasibility and effectiveness of these schemes in settings outside high-income countries. This study will examine the effectiveness of a scheme to refer hypertensive patients identified in Primary Health Care facilities (PHCU) of the Mexican social security institution to a group PA program offered in the same institution.

**Methods and design:**

We will describe the methods of a cluster randomized trial study designed to evaluate the effectiveness of an exercise referral scheme to increasing physical activity in hypertensive patients compared to a non-referral scheme. Four PHCU were selected for the study; the PHCU will take part as the unit of randomization and sedentary hypertensive patients as the unit of assessment. 2 PHCU of control group (GC) will provide information to hypertensive patients about physical activity benefits and ways to increase it safely. 2 PHCU of intervention group (IG) will refer patients to sports facilities at the same institution, to follow a group-based PA program developed to increase the PA levels with a designed based on the Transtheoretical Model and Social Cognitive Theory. To evaluate the effects of the intervention as well as short-term maintenance of the intervention’s effects, PA will be assessed at baseline, at 24 and 32 weeks of follow-up.

The main outcome will be the difference before and after intervention in the percentage of participants meeting recommended levels of PA between and within intervention and control groups. PA will be measured through self-report and with objective measure by accelerometer.

**Discussion:**

This study will allow us to evaluate a multidisciplinary effort to link the primary care and community-based areas of the same health care system. Our findings will provide important information about the feasibility and effectiveness of an exercise-referral scheme and will be useful for decision-making about the implementation of strategies for increasing PA among hypertensive and other clinical populations in Mexico and Latin America.

**Trial registration:**

Clinicaltrials.gov Identifier: NCT01910935. Date of registration: 07/05/2013.

## Background

The benefits of physical activity (PA) on health have been well documented [1-3]. However, a large proportion of the world population fails to meet current global physical activity recommendations (at least 150 minutes of moderate-to-vigorous PA/week) [4]. In 2010 the global prevalence of inactivity was estimated at 32%, and as much as 40% of the population in the Americas [5]. In Mexico, the prevalence of physical inactivity has increased 6%, from 13.4% to 19.4% in only six years [6].

Globally, the magnitude of the physical inactivity problem is worse in poorer regions of the world. For example, until 80% of mortality due to NCD’s and physical inactivity occurs in lower-middle income countries.^7^ As part of the strategies developed to prevent and control NCDs, Mexico’s Social Security Institution (MSSI), which covers 49.2% of the Mexican population, is providing comprehensive health care and referrals for PA programs for patients [7]. However, 16.8% are physical inactive and in a whole 83% of do not meet PA recommendations [8].

Increasing physical activity to recommended levels would help eliminate 6% to 10% of the major Non-Communicable Diseases (NCDs), including coronary heart disease (CHD), type 2 diabetes, breast and colon cancers [9]. Physical inactivity contributes to and aggravates NCDs like hypertension (HTN), [10] which constitutes the leading cause of NCD visits at the MSSI, [11] and the proportion of newly diagnosed MSSI patients with HTN has increased by 30% in only five years [12]. Complications associated with HTN consume between 6 and 8% of the total health care expenditure of the Mexican health system [11,13]. Adding physical activity to the HTN medical treatment paradigm for HTN can help control blood pressure, reduce mortality and complications and help curb the health care [14].

The Primary Health Care (PHC) setting has been identified as a base for PA-promotion strategies since it is a point of contact with hypertensive patients, and since basing interventions there would facilitate the continuity of care and integration of multiple disciplines into treatment [15]. PHC physicians have been seen as source of health promotion and powerful agents for physical activity promotion [16]. However, through the years strategies focusing exclusively on physician involvement have had little success. Insufficient health promotion training, lack of time of medical consultation, and lack of physician confidence that their recommendations for healthy lifestyles are useful for patients, has been the aim barriers to achieve it [17-19]. Therefore, it appears that PA counseling and PHC-based PA-referral schemes as an inclusive strategy utilizing available staff and facility resources to help people to become physically active might function better in this settings, since both have proven effective in helping inactive people to meet PA recommendations [20-22].

Systematic reviews of exercise-referral schemes demonstrate that challenges remain in terms of increasing patients’ acceptance of and adherence to PA programs [19-23]. However the results of these studies are from high-income countries, and little is known about effective ways to increase PA in countries with different income levels. These lower income countries are the focus of only 10% of the global research but house 90% of the world’s population [24]. If lifestyle changes such as increasing PA practice are to be implemented worldwide, it is essential to understand the mechanisms underlying the behavior of diverse populations.

In the context of studies about effectiveness of PA-referral schemes, to date there is lack of proven evidence of its effectiveness with objective outcome measures of PA [25], since interventions’ effects have been documented exclusively by self-report [21,26]. Therefore, this study will estimate the effectiveness of PA referral scheme with an objective PA assessment. This will be the first study of PA-referral scheme for chronically ill patients in the Mexican Health System.

The aim of this study is to evaluate the effectiveness of an MSSI PHC-based physician to a PA- referral scheme designed to help chronically ill patients to increase PA, in order to perform recommended levels of PA (150 minutes at week of moderate to vigorous intensity).

## Methods and design

### Setting

The Mexican Social Security Institute (MSSI) includes offices for primary, secondary and tertiary health services as well as facilities designed to develop PA programs (sports fields, gyms, pools and outdoor spaces for PA) called Social Security Centers (SCC). The SCC have specialized staff to guide and assist on promotion and practice PA in all potential participants.

### Design and recruitment process

This is a cluster randomized trial, with the primary health care unit (PHCU) as the unit of randomization and hypertensive patients as the unit of assessment, to evaluate the impact of a PA-referral scheme to help patients increase their PA levels and meet recommended PA guidelines. Four MSSI PHCU facilities will be assigned in a randomized way to intervention (2 PHCUs) and control groups (2 PHCUs). In all PHCUs, primary care physicians will identify hypertensive patients based on the following criteria: women and men with MSSI affiliation, between 35 and 70 years old, less than 5 years from hypertension diagnosis and/or without pharmacological treatment self-reporting willingness to engage in a PA program but currently not meeting PA recommendations (< 150 minutes per week of moderate to vigorous intensity PA). Using a standardized protocol, physicians will quickly screen for these criteria and will refer eligible patients to the study suite, located in the same PHCU facility. Trained staff will verify that potential participants meet the inclusion criteria described below, to confirm that they can safely engage in the PA program.

Inclusion criteria:

a) Adults between 35 and 70 years old; b) both sexes; c) patients with hypertension diagnosis within five years or less and/or without pharmacological therapy for hypertension (according with JNC 7 criteria) [27]; d) Not meeting PA recommendations (<150 minutes at week of moderate or vigorous intensity), as measured with the short-form of the International Physical Activity Questionnaire (IPAQ) [28]; e) currently in the contemplation or preparation stage for PA, according to Transtheoretical model of behavioural change [29]; f) low to moderate level of cardiovascular risk, according to the Guidelines for exercise testing and recommendations of the American College of Sports Medicine (ACSM) [30]. A pre-participation screening questionnaire from American College of Sports Medicine (ACSM) and ACSM [31], will be used to evaluate health status, medical history of cardiovascular, metabolic or lung disease, signs or symptoms suggestive of these conditions and number of cardiovascular risk factors. Symptoms that require a complex evaluation will be confirmed by medical staff; g) blood pressure levels: systolic blood pressure levels ≤ 160 mm Hg or diastolic ≤ 100 mm Hg [32,33]; [h) Body Mass Index < 35; i) biochemical markers in the following ranges: total cholesterol ≤ 240 mg/dL, fasting glucose level ≤ 126 mg/dL, triglycerides ≤ 150 mg/dL; j) physical ability to participate in the PA program (without problems that may impede walking or other moderate intensity PA).

Exclusion criteria:

For both the control and intervention groups: currently reporting high levels of PA (> 300 minutes at week of moderate to vigorous intensity) [34], having previously attended a PA program at MSSI facilities. Criteria during PA sessions in the intervention group: systolic/diastolic blood pressure prior to PA sessions > 200/100 mm Hg or during the session > 250/115 mm Hg. The elimination criteria proposed are: less than 80% PA program attendance with or without incomplete information in one of the three data-collection points in the study.The study’s recruitment process is schematized in Figure 1. Patients who meet the criteria previously described will be invited to participate. Patients accepting to participate will provide informed consent and will be formally enrolled.

**Figure 1 F1:**
[figure not shown]
Recruitment flowchart.

### Randomization

Randomization will be performed before other study activities, and conducted at MSSI facilities outside the PHCUs to avoid contamination. The 4 PHCUs were randomized into the intervention group (IG; 2 centers) and control group (CG; 2 centers) using sealed envelopes by a health researcher who was not involved in this study. To avoid contamination, that PHCUs selected, are on average 5.5 kilometers (kms) from the place where patients will be referred (IG at 5.1 kms. and CG at 6.6 kms.), within the urban area of the city and public transportation available, average transfer time is 20 to 30 minutes.

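### PHCUs are allocated before patients are recruited, and the article states nothing that hides the arm until enrolment, so recruitment may differ by arm

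*Protocol article*

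**What the plan says.** The Randomization section gives the order: "Randomization will be performed before other study activities". It then describes the allocation: "The 4 PHCUs were randomized into the intervention group (IG; 2 centers) and control group (CG; 2 centers) using sealed envelopes", done by a researcher outside the study.

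Recruitment is set out under Design and recruitment process. The work is done inside the allocated units: "In all PHCUs, primary care physicians will identify hypertensive patients based on the following criteria". Following a standardised protocol, "physicians will quickly screen for these criteria and will refer eligible patients to the study suite". Trained staff there check the inclusion criteria. Patients who qualify are then invited, give consent and are enrolled.

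Several criteria depend on what the patient says about intention or behaviour. The physician's screen includes "self-reporting willingness to engage in a PA program but currently not meeting PA recommendations". The inclusion list adds "currently in the contemplation or preparation stage for PA", activity below the guideline by the short IPAQ, and "physical ability to participate in the PA program".

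The abstract states what follows in the intervention arm: "2 PHCU of intervention group (IG) will refer patients to sports facilities at the same institution". Control PHCUs give information and usual care.

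Under Statistical analysis, the plan includes a baseline comparability analysis, the baseline value of each dependent variable in its model, and adjustment of the primary outcome for access, finances, scheduling, social support and patient conditions such as fitness or injury.

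**The concern.** Sealed envelopes protect the allocation of PHCUs. They do not protect the selection of patients within PHCUs, because that comes later. If the people who recruit, or the patients who decide, know the arm, the arms can differ in motivation before treatment starts.

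The criteria make this plausible. A patient asked about willingness may answer differently when the offer is three supervised sessions a week for 24 weeks than when it is advice and follow-up visits. Intervention sites also have a reason to favour likely attenders that control sites lack: each exercise group needs at least five patients to start, and attendance below 80% is listed as an elimination criterion.

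The primary outcome is whether a patient reaches the activity guideline, so motivation at entry bears directly on it. A difference in motivation produced by recruitment would be counted as an effect of the referral scheme.

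**Working it through.** The plan states no figure for this bias, so there is none to reproduce. The check is a reading of the sequence, followed by an illustration under stated assumptions.

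**1. Order of events**

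| Step | Who acts | Place in the article |
|---|---|---|
| PHCUs allocated | Outside researcher | Randomization |
| Patients identified and screened | Physicians of the allocated PHCUs | Design and recruitment process |
| Eligibility verified | Trained staff in the same PHCU | Design and recruitment process |
| Invitation, consent, enrolment | Patient | Design and recruitment process |

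Everything from the second row on comes after allocation.

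**2. Is the arm hidden?** The article does not say so for physicians, verifying staff or patients. It does not say that they know it either. The abstract has intervention PHCUs making the referral to the sports facilities, which makes knowledge likely there. For control PHCUs there is no comparable indication. The physician's own step, sending the patient to the study suite, is described identically for all four PHCUs, so that step does not require knowledge of the arm.

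**3. What the stated safeguards can do**
- The standardised screen and staff verification remove patients who do not qualify. They cannot recover eligible patients who were not referred or who declined because of the arm.
- The comparability analysis sees only measured variables in those enrolled.
- Baseline adjustment works where the baseline value varies. Inclusion requires less than 150 minutes a week on the IPAQ, so the IPAQ binary variable is *not active* for everyone. A constant carries no information on who is more motivated. Accelerometer values can vary at baseline and can help.
- The listed covariates cover fitness, injury and social support. Stage of change is recorded at baseline but is not listed.

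**4. Illustration of size.** Suppose preparation-stage patients reach the guideline at follow-up more often than contemplation-stage patients by a gap *g*, and the share of preparation-stage patients differs between arms by *d*. Before any adjustment,

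spurious difference = *d* × *g*.

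Neither input is in the documents; both are assumed to lie between 10 and 30 points.

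| *d* | *g* | *d* × *g* |
|---|---|---|
| 0.10 | 0.10 | 1 point |
| 0.20 | 0.20 | 4 points |
| 0.30 | 0.30 | 9 points |

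**5. What such a shift does to a test.** Assume no true effect, a control rate of 17% (the Sample size section's baseline figure), selection that raises the intervention rate by *s*, and a two-sided 5% test of two proportions with clustering ignored. The chance of a false result favouring the intervention is

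1 − Φ[(1.96 × SE₀ − *s*) / SE₁],

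with SE₀ = √(2p̄(1 − p̄)/n) and SE₁ = √((p₁(1 − p₁) + p₂(1 − p₂))/n).

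For *s* = 0.05 and n = 68: p̄ = 0.195, SE₀ = 0.0680, SE₁ = 0.0678, and (0.1332 − 0.05)/0.0678 = 1.23, which gives 11%.

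| *s* | 68 per arm | 112 per arm |
|---|---|---|
| 0 | 2.5% | 2.5% |
| 3 points | 6.5% | 8% |
| 5 points | 11% | 15% |
| 10 points | 29% | 44% |

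These figures show sensitivity. They do not estimate what will happen.

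**The case against.** The strongest reply is that this argues from silence. The article condenses a fuller protocol, and its recruitment flowchart (Figure 1) is not available here. Invitation wording, the moment patients learn their arm, and screening logs may be set out elsewhere. No sentence says that the screening physician knows the arm, and the abstract does not place the referral to the sports facilities before enrolment. This stands, and it limits the point to a risk. What remains is the sequence, which the article does state, and which clinic-level envelopes cannot protect.

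Second, the plan has real safeguards: the same screen in all PHCUs, verification by trained staff, and many criteria that are measured or instrument-based (blood pressure, BMI, laboratory values, the risk questionnaire). Physical ability is tied to problems that impede walking. The willingness criterion has the same wording everywhere. This narrows the opening for bias to the criteria that rest on self-report and to the decision to consent; it does not close it.

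Third, the analysis already adjusts for baseline values and patient conditions. This is right for the model of activity minutes and for the fitness pathway. It fails for the IPAQ binary outcome, whose baseline value is constant.

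Fourth, the magnitude rests on assumed inputs, and even its upper end of 9 points is under half the 20-point threshold. That also stands.

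**Conclusion.** The point holds as a risk of differential recruitment, of unknown size, that the planned adjustment covers only in part. It rests on three facts in the article: allocation precedes identification of patients, no concealment until enrolment is stated, and some entry criteria are self-reported and close to the outcome. The range of 1 to 9 points is an illustration that depends on the assumed stage imbalance and follow-up gap, before any adjustment.

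Three stronger readings are not supported. A reader might infer that physicians know the arm and choose patients accordingly; the article does not say this, and describes one common physician step. A reader might infer that selection alone could produce the 20-point effect; the illustration does not reach it. A reader might also add that two PHCUs per arm make the bias inseparable from an effect; having so few clusters is a separate weakness that would exist under any order of recruitment.

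The change is worth making because it is cheap and acts on the primary comparison.

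**What to change.** - Use the same invitation wording in all four PHCUs.
- Tell patients their arm only after consent and the full baseline assessment. The functional capacity test that the Implementation section places in the first programme session would have to follow disclosure.
- Add baseline stage of change and continuous baseline accelerometer minutes to the binary primary-outcome model. Both are already collected.
- Report the numbers screened, eligible, consenting and refusing for each PHCU, so that readers can see whether recruitment differed.

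Costs: the consent wording needs ethics approval. Because accelerometers are worn for seven days, disclosure would come at least a week after the first visit. Enrolment depends on patient flow, so clinic staff may learn the arm over time, and masking will be incomplete. Some intervention patients may decline the programme after baseline and, kept in the intention-to-treat set, dilute the effect. Some control patients may leave on learning their arm, in a trial that already expects high dropout. The log and the two covariates keep their value even where masking fails.

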#### Baseline assessment

During this assessment a questionnaire will be administered and functional capacity measurements will be taken. To evaluate the effects of the intervention, measurements will be taken at baseline, at 24 weeks of study entry baseline, to assess adherence to the intervention, and at 32 weeks of study entry, to determine short-term maintenance of the intervention’s effects. Details of study’s design and flow chart are showed in Figure 2. A trained nurse, part of the research team, will carry out this assessment, duration between 40 to 60 minutes.

**Figure 2 F2:**
[figure not shown]
Study design flowchart.

### Control group (CG)

Participants in the control group will be informed about health benefits of PA and a balanced diet, and how to safely increase PA levels. Patients in this group will continue receiving their usual care at PHCU facilities. The control group will be invited to undergo two subsequent PA assessments at the PHCU facilities at 24 and 32 weeks of follow-up. The research team will keep in contact with these patients during monthly doctor’s appointment or through a monthly phone call to emphasize the participation in the study and with appointment reminders at weeks 22 and 30.

### Intervention group (IG)

The group-based PA program developed to increase the PA levels of hypertensive patients was designed based on the Transtheoretical Model [29] and Social Cognitive Theory [35,36].

The components of the 24 week PA program are: duration (60 minutes per session), frequency (3 times per week), and intensity (moderate to vigorous). The program will be conducted and supervised by trained staff with experience in handling groups of patients with chronic conditions like diabetes and hypertension; therefore, only typical embodiments of exercise like dancing, supervised walking and swimming will be included.

### Implementation

Patients in the IG, will be invited for following activities during the first three sessions of the PA program at the SCC:

1) Select and enroll in their PA group. Each group will start with a minimum of 5 patients and a maximum of 20. Therefore, between 6 and 8 new groups may open during the intervention, depending on the flow of participants. Patient groups were organized based on personal preferences of exercise and for patients with joint or bone problems, swimming will be recommended.

2) During the first session, MSSI staff trained in guiding the PA program will administer the functional capacity test, to personalize the PA prescription and determine the PA intensity each patient will be instructed to exercise at the start of the program. PA intensity will be increased gradually, depending on patient characteristics and training progression for each patient. PA prescription will start at 55% of the patient’s maximum heart rate (MHR), and gradually increase to 75% of MHR to enhance safety and efficacy. The trained staff will instruct patients how to monitor their heart rate before, during and after PA sessions and to be alert to fluctuations outside the ranges. A general description of the PA program progression follows.

**Level 1 or induction:** between the initial 4 to 6 weeks, during which the patients will adopt a regular exercise habit.

**Level 2 or development:** during weeks 7 to 12 in which there will be a gradual increase in exercise volume (duration and intensity) every 2 weeks.

**Level 3 or maintenance:** beginning at the 13th week, when the patient has started to reach an improved level of functional capacity and exercise tolerance, allowing him or her to maintain the same routine in duration and intensity during group-based exercise classes, while improving free-living and other recreational PA as part of their lifestyle sessions the following weeks.

3) The group-based PA sessions will consist of three stages: warm-up, predominantly aerobic exercise, and recovery. The components of PA program are shown in Table 1. The trained staff will also record participants’ self-reported recreational PA outside the SCC.

**Table 1 T1:** Components of physical activity program

**Physical activity phases**	**Level 1 induction (Week 2-6) duration, target intensity**	**Level 2 development (Week 7-12) duration, intensity**	**Level 3 maintenance (Week 13-23) duration, intensity**
**Warm-up phase:** Involving all parts of the body: neck, upper limbs, lower limbs	10 minutes, 50% of MHR	10 minutes, 50% of MHR	10 minutes, (MHR) 50%
**Aerobic phase:** Walking, running, dancing or bicycling.	20 minutes (THR) 55%	30 minutes (THR) 55-75%	40 minutes (THR) 60-75%
**Recovery phase:** Gradually reduce the intensity. Stretch, bend and rotate body parts starting with the neck and concluding with the ankles, emphasizing deep breathing.	5-10 minutes	5-10 minutes	5-10 minutes

MHR: Maximum heart rate (220-age). THR: Training Heart Rate.

Reference: Fox III, SM Naughton, JP and Haskell, WL. *Physical activity and the prevention of coronary heart disease. Ann Clin Res* 1971; 3:404-432.

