### Statistical analysis

Analysis of effectiveness will be carried out according to an intention to treat analysis.

A baseline comparability analysis will be carried out among the IG and CG, in relation to the variables studied during the three measurement points in the study (0, 24 and 32 weeks). To compare means, T-test or analysis of variance will be conducted, while Mann–Whitney tests will be used to compare variables without a normal distribution. Analysis of covariance will be conducted to assess variables with repeated measures along the study.

Longitudinal generalized mixed models will be developed to account for the repeated measurements (0, 24 and 32 weeks) for each patient. These models will be linear for continuous changes in PA (minutes), and logistic for categorical PA variables.

For the primary outcome variable, models will be adjusted for potential confounding variables that may alter the proportion of patients who meet the minimum recommendation for PA: a) geographic accessibility barriers (e.g. distance to SCC); b) financial (e.g. self-report of financial resources to pay for transportation); c) administrative (e.g. SCC schedules not being compatible with patient’s reported schedules); d) social support (e.g. help with transportation to the SCC); e) conditions of patient (for example: greater physical fitness than other hypertensive patients, discomfort or injury discouraging participation in the program, presence of acute or chronic diseases).

In order to minimize regression bias to the estimated mean, baseline values for each dependent variable will be included in each regression model [47].

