Evidence from self-reports indicates that referral schemes are effective in increasing PA as measured by self-reports. Yet, information on referral programs’ influence on patient’s PA, measured via objective method is lacking [22,54]. This study will be the first to use direct measurements of PA to show the effects of an exercise-referral scheme in real-world settings. Although we are aware of the limitations posed by the study’s short duration, this does not compromise its utility for physical activity promotion in patients with chronic conditions.

If this intervention is found to be effective, the information could useful to optimize resources. For example, to design programs according to different stages of change, proposing differentiated actions for patients in each one of the stages, as stated in the transtheoretical model [29]. Namely, carry out actions to encourage the willingness to change for patients in pre-contemplation stages or to strengthen their physically active behavior for patients in maintenance stage.

The study population is sharing characteristics such as initially sedentary lifestyle, willingness to engage in PA, and recent hypertension diagnosis. Sharing these traits could encourage the group to develop a sense of community which would promote self-efficacy and social support [55], a fundamental feature of successful behavior change according to social cognitive theory [35,36].

To ensure the quality of this study, the clinical trial guidelines developed by the CONSORT group will be followed [56]. We will be able to identify the number of patients at the three measurement phases of the study and conduct the analysis according to intention to treat.

Finally, this assessment of effectiveness in the real-life conditions of the IMSS health and social services facilities, will serve as a baseline for these types of intervention studies in the context of Latin America, where the ability to test the feasibility, adherence and sustainability of an exercise-referral scheme has not been explored.

While this study is an effort to try to improve participants’ health and the quality of life through PA promotion, we are aware that this kind of initiative does not address the root causes of physical inactivity. This problem will persist unless both PA behaviors and the causes of inactivity change, a situation which requires approaches focused not only on individual behavior, but also on complex population-level systems and interactions [57].

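### Only the intervention arm is treated in exercise classes, and the stated model names no class effect; any shared class effect makes its standard error too small, by an amount the protocol does not fix

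*Protocol article*

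**What the plan says.** Under Implementation, intervention (IG) patients choose and join a class: "Each group will start with a minimum of 5 patients and a maximum of 20", and "between 6 and 8 new groups may open during the intervention, depending on the flow of participants". On how classes form: "Patient groups were organized based on personal preferences of exercise".

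Control (CG) patients receive information and no classes: "Patients in this group will continue receiving their usual care at PHCU facilities" (Control group).

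Under Statistical analysis, the generalized "mixed models will be developed to account for the repeated measurements (0, 24 and 32 weeks) for each patient". They are linear for minutes of activity and logistic for meeting the recommendation. Neither that section nor Sample size names a term for exercise class or for the PHCU, although the PHCU is the randomized unit, with two per arm.

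**The concern.** Treatment in groups can make the outcomes of group members alike, through a common timetable, activity and social process. Here that can happen in one arm only. The Discussion gives a reason to expect it: shared traits "could encourage the group to develop a sense of community which would promote self-efficacy and social support". A model that handles correlation only within a patient treats class-mates as independent.

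At stake are the standard error of the IG result, the confidence interval for the arm difference and the error rate of the primary test. There is also a question of how far a PHCU term would help. It covers class effects if each class draws on one PHCU, but not if classes mix patients from both IG PHCUs.

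**Working it through.** **Inputs from the protocol article.** 112 patients enrolled per arm, 68 per arm before the dropout allowance, 17% against 37% meeting the recommendation, alpha 0.05 (Sample size); 6 to 8 classes of 5 to 20 (Implementation); two PHCUs per arm (Randomization).

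**Assumptions.** Within-class ICC of 0.01, 0.05 or 0.10 (the article gives none), equal class sizes, normal approximation, two-sided test.

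**The plan's own figure.** The article has no design effect or ICC to reproduce. Its 68 per arm does not reproduce from the stated inputs either (102 two-sided, 83 one-sided, without continuity correction). That is a separate matter and does not bear on this point.

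**Class size.** m = 112/8 = 14.0 to 112/6 = 18.7. With 68 patients, m = 68/8 = 8.5 to 68/6 = 11.3. Both ranges fit within 5 to 20.

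**Formulas.** Design effect in the IG only: DE = 1 + (m - 1) × ICC. The true IG standard error is sqrt(DE) times the one that ignores classes. With the same proportion in both arms, the standard error of the difference grows by f = sqrt((DE + 1)/2), and the true type I error is 2 × P(Z > 1.96/f).

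Worked case, m = 14, ICC 0.05: DE = 1 + 13 × 0.05 = 1.65; f = sqrt(2.65/2) = 1.151; 1.96/1.151 = 1.703; type I error 8.9%.

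| IG patients in classes | ICC | DE | IG standard error ratio | Type I error |
|---|---|---|---|---|
| 112 | 0.01 | 1.13-1.18 | 1.06-1.09 | 5.8-6.0% |
| 112 | 0.05 | 1.65-1.88 | 1.28-1.37 | 8.9-10.3% |
| 112 | 0.10 | 2.30-2.77 | 1.52-1.66 | 12.7-15.3% |
| 68 | 0.05 | 1.38-1.52 | 1.17-1.23 | 7.2-8.1% |

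**Power.** With 112 per arm, 17% against 37% and ICC 0.05, the standard error of the difference is sqrt((0.2331 × DE + 0.1411)/(0.2331 + 0.1411)) = 1.19 to 1.25 times the unclustered value. Power falls from about 93% to 79-83%.

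**Dilution by non-attenders.** Suppose all 112 IG patients are analysed but only 68 ever join a class (an illustration, not a figure from the article). Then DE = 1 + (68/112)(m - 1) × ICC. At ICC 0.05 with m = 8.5 to 11.3, DE is 1.23 to 1.31 and the type I error is 6.3-6.8%.

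**Comparison with the PHCU.** With 112/2 = 56 patients per PHCU and an assumed PHCU ICC of 0.01 to 0.05, DE = 1 + 55 × ICC = 1.55 to 3.75 in both arms. The type I error of an analysis that ignores the PHCU is 2 × P(Z > 1.96/sqrt(DE)) = 11.5-31%. That is the larger gap.

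**When a PHCU term is enough.** Take k IG classes with class variance c, PHCU variance u, residual variance e and n IG patients split equally between the two PHCUs. In both layouts below, the variance of the IG mean is u/2 + c/k + e/n.

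- *Classes nested within PHCU:* each PHCU mean has variance u + c/(k/2) + e/(n/2), and the two are independent. Half the variance observed between them estimates u/2 + c/k + e/n, so class effects are included.
- *Classes shared evenly by both PHCUs:* class effects enter both PHCU means alike and cancel from their difference. The same estimate gives only u/2 + e/n and misses c/k.

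**The case against.** The strongest reply is that this is silence rather than error. The article does not say that patient is the only random effect, and a class term could sit in an analysis plan that is not shown. That stands as a limit on the wording: the article names one source of correlation and no other. It does not remove the point, because an analysis built to that description leaves class out.

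Second, the missing PHCU term is the larger fault, and a PHCU-level analysis would absorb class effects if classes are nested. This stands, and it makes the point secondary.

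A reader might infer that the two IG PHCUs do share classes, since Randomization gives distances "from the place where patients will be referred", in the singular, and classes form by preference. The documents do not settle it: that sentence is about distance and contamination, and the Abstract speaks of sports facilities in the plural.

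A reader might also infer strong correlation from a common instructor, or from like patients choosing the same class. The article mentions trained staff but does not say that each class keeps one instructor. Sorting of independently enrolled patients does not by itself inflate the variance of the IG mean; only an effect that the class imposes on its members does. The group in the Discussion passage may mean the study population rather than a class. Personalized exercise intensity and a whole-week activity outcome could both weaken a class effect.

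Finally, the ICC is assumed, and at 0.01 the effect is slight. That stands too. In the other direction, unequal class sizes would raise the design effect.

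**Conclusion.** The point holds, with limits. Treatment in classes occurs in one arm, the stated model does not allow for it, and for any positive shared class effect the standard errors of the IG result and of the arm difference are too small. The direction does not depend on the ICC, but the size does: close to negligible at 0.01, material at 0.05 or above. The upper figures further assume that all 112 IG patients belong to a class, so the 13-15% should not be read as the expected error rate of this trial. The number of classes is itself only what the article says may open.

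The point ranks below the missing PHCU term, and a class term alone would not repair the analysis. Once the PHCU is handled correctly, class is a separate problem only if the two IG PHCUs share classes.

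**What to change.** - Record each IG patient's class. Attendance is already due to be entered in the study database (Data management), so this is at most one added variable.
- State whether patients from the two IG PHCUs attend the same classes.
- Analyse with the PHCU as the randomized unit and degrees of freedom suited to two clusters per arm.
- Add a class effect in the IG only (a partially nested model). If the full logistic longitudinal model cannot be estimated with two PHCUs per arm, report the class effect as a sensitivity analysis.

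The cost is analysis wording and one variable, with no change for patients. The downsides are wider intervals, a class variance that 6 to 8 classes estimate imprecisely, and a harder model to fit if classes cross PHCUs.
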